## Abstract

**Background:** Allergic rhinitis (AR) is an upper airways chronic inflammatory disease mediated by IgE, which affects 10%–20% of the population. The mainstay for allergic rhinitis nowadays include steroids and antihistamines, but their effects are less than ideal. Many patients therefore seek Chinese medicine for treatment and Yupingfeng Powder is one of the most common formulae prescribed. In this study, we aim to investigate the efficacy and safety of Yupingfeng Powder with variation for the treatment of allergic rhinitis.

**Study design:** This is a double-blind, randomized, placebo-controlled trial. A 2-week screening period will be implemented, and then eligible subjects with allergic rhinitis will receive interventions of either “Yupingfeng Powder with variation” granules or placebo granules for 8 weeks, followed by post treatment visits at weeks 12 and 16. The change in the Total Nasal Symptom Score (TNSS) will be used as the primary outcome.

**Discussion:** This trail will evaluate the efficacy and safety of Yupingfeng Powder in treating allergic rhinitis. The study may provide the solid evidence of Yupingfeng Powder with variation can produce better clinical efficacy than the placebo granules.

**Trial registration:**
ClinicalTrials.gov, identifier NCT04976023.

## 1 Introduction

Rhinitis, is a common disease generally defined as the inflammation of the nasal mucosa, affecting up to 40% of people (Small et al., 2007). The most common chronic rhinitis is allergic rhinitis (AR), which is affecting 10%–20% of people, and its prevalence is increasing globally (Dykewicz and Hamilos, 2010). AR can occur at any age and its occurrence is known to be related to patients’ living habits and environment (Wu and Mei, 2010; Li, 2015). Severe AR may affect quality of life, sleep and work performance of the patients (Dykewicz and Hamilos, 2010).

AR is an upper airways chronic inflammatory disease mediated by IgE, and the typical symptoms are sneezing, rhinorrhea, nasal itching, and nasal obstruction. AR is difficult to cure, and its relapse rate is also very high. If the condition is left untreated, it may give rise to various complications, such as sleep disturbances, general fatigue, loss of appetite, loss of attention and learning difficulty (Chen, 2013; Li, 2015).

The development of AR involves several factors, including the environment, immune system, and genetic susceptibility. Several types of cells, cytokines, and chemokines play important role in the allergic inflammation. Cytokines are responsible for mediating allergic inflammation, and the T helper cell (Th) 2 cytokines is essential in both the development of allergic sensitization and pathology of allergic inflammation (Maes et al., 2012). It has been shown that Th1-type cells are predominant in healthy subjects, while Th2-type cytokines are predominant in the nasal mucosa and epithelial tissues of AR subjects (Zhu and Paul, 2008). AR is a result of disequilibrium of Th1 and Th2 cytokines, for which Th2 is predominating over Th1 cells. Moreover, regulatory T-cell (Tregs), another subtype of T-cell, suppresses both the expression of Th1 and Th2-type cytokine (Akdis et al., 2006). And so, it has been suggested that there is an imbalance of Th2 and Treg-cell in AR patients (Sin and Togias, 2011). On the other hand, Tregs also restrict both Th1 and Th2 cell-mediated inflammation. The lack of Tregs may cause the happening of allergic inflammation with the increase of Th2 cytokines (Hawrylowicz and O’Garra, 2005). By synthesizing interleukin-10 (IL-10) and the transforming growth factor-β (TGF-β), Tregs can bring the allergic inflammation under control (Akdis et al., 2005). An allergen-specific functional defect of Treg is happening in AR patients, in whom the Tregs can promote the polarization of Th2, and consequently the synthesis of IgE (Han et al., 2010). IFN-γ, a characteristic cytokine produced by Th1 cells, is essential in bridging the innate and the adaptive arms of the immune system. In addition, IFN-γ is a key cytokine in the regulation of local leukocyte-endothelial interactions (Akkoc et al., 2008).

A previous study showed that a subset of CD4^+^ T cells, Th17 cells, is also important in the pathogenesis of allergic diseases (Fujiwara et al., 2007), which renders a new mechanism underlying the occurrence of AR. Th17 cell is responsible for the production of various cytokines, including IL-17, IL-6, TNF-α, and IL-22 (Schmidt-WeberCarsten et al., 2007; Wang and Liu, 2008). Studies suggests that during the acute phase of allergic reaction, neutrophilic infiltration may occur with Th17. IL-17 was found to involve in the induction of allergen-specific Th2 cell activation, eosinophil accumulation, and serum IgE production, thus suggesting IL-17A can regulate the established Th2-driven allergic immune response (Oboki et al., 2008). It has been found that serum IL-17 responses are correlated with the symptom severity scores, medication use, and peripheral eosinophil counts in AR patients (Ciprandi et al., 2008; Ciprandi et al., 2009). IL-10 is an important natural immune regulator and mainly produced by Th2 cells. It can inhibit the antigen-presenting effects of macrophages and the proliferation of active T cells, and suppress the intensity of inflammation (Wu et al., 2001; Levings et al., 2002).

In general, AR is a complicate immune and inflammatory disease. Its pathogenesis is not fully known yet, and there is no cure for this common allergic disorder (Zhou and Lu, 2010; Ni, 2011). Nowadays, the mainstay treatments for AR include steroids to reduce inflammation and swelling, and antihistamines to block the action of histamine (Ni, 2011). However, many clinical studies have found that the treatment effect of conventinal medicines is often undesirable, usually with adverse effects, such as nasal itching and frequent sneezing (Peng, 2014; Chen, 2015). Therefore, there exists a need to find a more effective and safer alternative for the treatment of AR.

Chinese herbal medicine (CHM) is a popular choice for AR patients seeking complementary and alternative therapies to reduce their clinical symptoms in East Asia (Chan and Chien, 2014; Kern and Bielory, 2014). Previous studies have shown that CHM could reduce nasal symptom, enhance quality of life, and strengthen body constitution in patients with AR (Luo et al., 2019). CHM appears to be a promising intervention for patients with AR. However, the previous studies had some methodological limitations, which weaken the clinical evidence for the efficacy of CHM. More scientifically methodological rigorous studies are needed to establish a solid evidence (Luo et al., 2019).

The core treatment principle of Chinese medicine are the syndrome differentiation and pattern identification. AR is in the disease category of “Rhinitis” in Chinese medicine. In the theory of Chinese medicine, this disease is resulted from the deficiency of Qi in lung, spleen and kidney, and is also due to the invasion of the external wind to the nasal orifices (Li, 2008; Zhou and Lu, 2010; Li, 2015). Therefore, according to tranditional Chinese Medicine (TCM) theory, the treatment principle of AR is to tonify the Qi of lung and spleen.

Yupingfeng Powder, composed of three Chinese herbs, i.e., *Astragalus mongholicus* Bunge [Fabaceae], *Atractylodes macrocephala* Koidz. [Asteraceae] and *Saposhnikovia divaricata* (Turcz. ex Ledeb.) Schischk. [Apiaceae], is commonly used for allergic diseases including AR (Yen et al., 2015). Clinical studies have shown that Yupingfeng Powder can improve symptoms of AR such as sneezing and nasal itching (Chan and Chien, 2014; Fang et al., 2014) and quality of life (Chan and Chien, 2014) and decrease the levels of interleukins like IL-4 and IgE in AR patients (Fang et al., 2014). A glucosidic extract of Yupingfeng Powder was found to have the ability to activate the T helper cells and regulate some subsets of T lymphocytes, which can exert anti-inflammatory and immunoregulatory (Gao et al., 2009).

Oral CHM influences the gastrointestinal system, including the gut microbiota and the intestinal mucosa. The gut microbiota has been found highly related to our health and various diseases (Frick and IngoAutenrieth, 2012). Studies show that certain probiotics can improve the symptoms of AR patients (Harissios et al., 2008; Nagata et al., 2010; Costa et al., 2014; Güvenç et al., 2016). Thus, we hypothesize that gut microbiota may be influenced by complex interplays with the CHM components, such as glycosides and oligosaccharides (Xu et al., 2017), in the same manner as an oral probiotic to achieve systematic immunological conditions by regulating local intestinal immunological conditions as shown in previous studies (Ivory et al., 2008; Levy et al., 2017).

In recent years, some clinical studies have found that Yupingfeng Powder can increase anti-allergic ability and improve body’s resistance with few side effects, such as feeling of abdominal distension or increase in acne (Chen, 2013; Chan and Chien, 2014), indicating the advantages of oral Chinese medicine in the treatment of AR. In this project, we designed a double-blind, randomized, placebo controlled clinical trial to assess the efficacy of Yupingfeng Powder with variation for AR patients with TCM syndrome of qi deficiency of lung and spleen, and to explore the molecular mechanism of Yupingfeng Powder in treating AR with respect to the modulation of immune response and gut microbiota.

## 2 Methods

### 2.1 Study design

This is a randomized, double-blind, placebo-controlled trial. A 2-week screening period will be implemented, and then eligible subjects with AR will receive either “Yupingfeng Powder with variation” granules or placebo granules for 8 weeks followed by a post treatment visits at weeks 12 and 16.

### 2.2 Study population

Potentially eligible subjects with AR will be screened for the following eligibility criteria:

#### 2.2.1 Inclusion criteria

• Aged 5 or above;• Subjects with deficiency of lung and spleen Qi, which will be determined by Chinese Medicine Practitioners (CMP). (There will be a checklist of 13 TCM symptoms, subjects with two or more of the symptoms will be determined as deficiency of lung and spleen Qi);• At least two or more allergic symptoms (rhinorrhea, sneezing, nasal obstruction and nasal itching) for a cumulative period greater than 1 h per day. These symptoms may be accompanied by itchy and red eyes and tears; and• Able to provide voluntary written informed consent.

#### 2.2.2 Exclusion criteria

• Known chronic disease such as asthma, rhinosinusitis, nasal polyposis;• Known severe medical conditions, such as cardiovascular, liver or renal dysfunction, diabetes mellitus, cancers, cerebrovascular diseases, blood system diseases;• Concomitant use of steroid, non-steroidal anti-inflammatory drugs (NSAIDs), anticoagulant, and immunotherapy within past month;• Impaired hematological profile and liver/renal function exceeds the upper limit of the reference value by two times;• Known alcohol and/or drug abuse;• Known allergic history to any Chinese herbal medicines; or• Known pregnant or lactating.

### 2.3 Study intervention

#### 2.3.1 Study treatments

The eligible subjects will be randomly allocated to receive either “Yupingfeng Powder with variation” granules (15.55 g twice daily) or placebo granules (15.55 g twice daily) for 8 weeks. Variable dosages will be adopted according to the age of subjects. The daily dosage of “Yupingfeng Powder with variation” consists of the following herbal formula: *A. mongholicus* Bunge [Fabaceae] (Huang-Qi) 20 g, *A. macrocephala* Koidz. [Asteraceae] (Bai-Zhu) 10 g, *S. divaricata* (Turcz. ex Ledeb.) Schischk. [Apiaceae] (Fang-Feng) 6 g, *Magnolia biondii* Pamp. [Magnoliaceae] (Xin-Yi-Hua) 10 g, processed *Xanthium strumarium* L. [Asteraceae] (Chao-Cang-Er-Zi) 8 g, *Ganoderma lucidum* (Chi-Ling-Zhi) 12 g, *Platycodon grandiflorus* (Jacq.) A.DC. [Campanulaceae] (Ji-Geng) 10 g, processed *Drgonsbones* (Duan-Long-Gu) 15 g, processed *Ostreae concha* (Duan-Mu-Li) 15 g, *Terminalia chebula* Retz. [Combretaceae] (He-Zi) 8 g, *Glehnia littoralis* (A.Gray) F.Schmidt ex Miq. [Apiaceae] (Bei-Sha-Shen) 10 g, *Cordyceps sinesis* powder (Chong-Cao-Jun-Si-Fen) 3 g, *Dictamnus dasycarpus* Turcz. [Rutaceae] (Bai-Xian-Pi) 10 g. The study drug will be prepared using single granules, with the ratio of 1:3 for *A. macrocephala* Koidz. [Asteraceae] and 1:5 for the others according to the granules preparation method of the Nong’s Company Limited, i.e., 1 g granule = 3 g decoction piece and 1 g granule = 5 g decoction piece respectively, except for *Cordyceps sinesis* powder which is in the ratio of 1:1. The above granules are all extraction by water of the crude plants.

The granules are commercially available. The quality control and production of Nong’s Company Limited comply with the GMP standards of the PRC, Australia and the USP. All the herbal medicines comply with the standards of Chinese Pharmacopoeia. There is also laboratory for quality control with ISO 17025 certificate.

One daily dose of “Yupingfeng Powder with variation” granules will be equally sealed into two packs, which will be dissolved in hot water and administered while it is lukewarm. Participants will take two times daily, one pack in the morning and another in the evening after meal. Those subjects aged 5–12 will take half of the total dose, and those aged 13 or above will take normal adult dose.

The placebo granules will be prepared from starch and an edible pigment and will be matched as closely as possible to the appearance and taste of “Yupingfeng Powder with variation” granules.

All study medications (“Yupingfeng Powder with variation” granules and placebo granules) will be produced by the manufacturer following good manufacturing practice. They will be packed at the Pharmacy of the Integrative Medical Center of the Hong Kong Institute of Integrative Medicine, The Chinese University of Hong Kong.

#### 2.3.2 Prohibited drugs

Anticoagulant agents, NSAIDs, steroids, antihistamine, immunotherapy, antibiotics, prebiotics, probiotics and Chinese herbal products which are used to treat AR are prohibited during the study period.

#### 2.3.3 Treatment compliance

Drug compliance is assessed by the number of doses taken during study period by subjects’ self-report.

### 2.4 Patient visits

#### 2.4.1 Screening visit

Information about the study, processing and scheduling will be explained before enrolment. Subjects will be screened within 14 days prior to treatment commencement. Medical consultation and assessment, medical history, vital sign and concomitant medication will be assessed and recorded. Blood samples for serum IgE, complete blood picture (CBP) with differentiation and renal and liver function will also be taken at screening visit. The screening assessment can be served as the baseline assessment. Informed consent will also be obtained after the study has been fully explained to each subject.

#### 2.4.2 Baseline randomization visit

Eligible subjects will have medical consultation and assessment by Registered Chinese medicine practitioner (CMP) investigators with at least 3 years’ clinical experience. Vital sign will be assessed, medical history and concomitant medications will also be recorded at baseline. TNSS, Rhinoconjunctivitis Quality of Life Questionnaire (RQLQ) score for aged 13 and above and Paediatric Allergic Disease Quality of Life Questionnaire (PADQLQ) score for aged 12 and Visual Analog Scale (VAS) for frequency and severity of AR episodes will be evaluated. Blood samples for serum cytokines (IL-10 and IL-17) will also be collected. Subjects will be randomly assigned (in a 1:1 ratio) to receive for 8 weeks of either “Yupingfeng Powder with variation” granules or placebo granules.

#### 2.4.3 Follow-up visit

CMP investigators with at least 3 years’ clinical experience will provide consultation under Chinese medicine theory, prescribe and dispense “Yupingfeng Powder with variation” granules or placebo in this trial. Subjects will return for follow-up at baseline, weeks 4 (±4 days) and 8 (±4 days), and followed by a post-treatment visit at weeks 12 and 16 (±4 days) (Table 1).

**TABLE 1 T1:** Study schedule.

Items	Screening	Treatment period			Post-treatment follow up	
	−14 to 0 days	Day 0 (baseline)	Week 4	Week 8	Week 12	Week 16
			(±4 days)	(±4 days)	(±4 days)	(±4 days)
Clinical assessment						
Informed consent	X					
Eligibility	X					
Medical consultation and assessment	X	X	X	X	X	X
Medical history	X					
Concomitant medication	X	X	X	X	X	X
Vital sign (BP/pulse)	X	X	X	X	X	X
AE/SAE assessment			X	X	X	X
Outcome assessment						
Total nasal symptom score (TNSS)		X	X	X	X	X
Visual analog scale (VAS)		X	X	X	X	X
Rhinoconjunctivitis Quality of Life Questionnaire (RQLQ) and Paediatric Allergic Disease Quality of Life Questionnaire (PADQLQ)		X	X	X	X	X
Serum level of IgE	X			X	X	
Serum levels of Cytokines (IL-10 and IL-17)		X		X	X	
Gut microbiota		X		X		
Laboratory assessment						
CBP with differentiation	X			X		
Renal and liver function test	X			X		
Intervention						
Administration of study drug		X	X	X		

### 2.5 Randomization and blinding

The eligible subjects will be randomly assigned to either experimental group or control group at the ratio of 1:1. A randomization schedule will be generated by computer to assign subjects to the treatment sequences. Concealment of allocation will be ascertained by an independent research staff, and identically designed treatment packs will be used for study drugs.

This is a double-blind randomized controlled trial. All study investigators and subjects will be blinded in the study. The random allocations will be put into opaque envelops with sequential study numbers. Two sets of the envelope will be prepared, with one set for randomization at the site, and another set for storage in the investigator’s office for emergency un-blinding.

### 2.6 Assessments

The changes of TNSS, RQLQ score for aged 13 and above and PADQLQ score for aged 5–12 and frequency and severity of AR episodes (VAS) will be evaluated at each study visit. Also vital sign and concomitant medications will be assessed and recorded. Subjects’ self-reported Chinese medicine adherence will be assessed, and reasons for skipping doses will be recorded.

Blood samples for serum cytokines (IL-10 and IL-17) will be collected at baseline, weeks 8 (±4 days) and 12 (±4 days). Stool specimen (within 24 h of the study visit day) will be collected at baseline and week 8 (±4 days). Subjects’ information will be kept anonymous.

Assessment of safety will be conducted by laboratory parameters and subjects’ reported adverse events and/or serious adverse events. The assessment of adverse event will be recorded according to CTCAE 4.0 which is a standard assessment tool. A direct telephone line will be provided so that subjects can report any adverse events during office hours between scheduled visits. The subjects will be recommended to attend Emergency Department at the nearest hospital beyond office hours if deemed necessary.

All subjects will be required to keep daily record for monitoring their compliance and side effects of the study treatment. Besides, they need to record 3 days of food diary before the day for taking stool specimens for gut microbiome analysis as the food intake may affect the gut species and influence the gut microbiome analysis result.

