### 3.2 Secondary outcomes

1. The change in the TNSS at weeks 4, 12, and 16.2. The changes in frequency of AR episodes and their severity VAS at weeks 4, 8, 12, and 16;3. The changes in the RQLQ score or PADQLQ score;4. The changes in the serum levels of total IgE and cytokines (IL-10 and IL-17) at weeks 8 and 12;5. The changes in the gut microbiota composition in stools at week 8; and6. Adverse events (graded by CTCAE) related to study treatment.

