### 4.2 Adverse events

An adverse event is any undesirable medical event occurring in the subject within the trial period, whether or not it is related to the study intervention. The assessment of adverse event will be recorded according to CTCAE 4.0 which is a standard assessment tool.

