### 5.2 Statistical analysis

Baseline data (gender, age, vital signs) will be descriptively summarized. Differences of measurement data between the groups will be assessed using *t*-test for normally distributed continuous variables and Wilcoxon signed rank test for non-normally distributed variables.

Measurement data of different groups in each visit will be reported as mean ± standard deviation (SD). Intra-group comparisons between baseline and each visit will be conducted by using paired *t*-test (or Wilcoxon signed rank test). Comparisons between groups will be conducted by using an analysis of variance (ANOVA), with other confounding factors like multicenter character conducting the covariate analysis. Statistical analysis for the data which do not meet above conditions (e.g., non-normal) will be conducted with the use of non-parametric test.

For AEs analysis, comparisons of the incidence rate of AEs between groups will be conducted with the use of χ^2^ test. The investigators need to list and describe the AEs occurred in this trial. If the data do not conform to χ^2^ test (data include 0, or theoretical frequency is below 5), Fisher’s exact test will be used.

For laboratory parameters, Spearman’s coefficient correlation will be used for comparison with different parameters and one way ANOVA test for significant correlation between groups.

All *p* values and 95% confidence intervals are two-sided, and *p* < 0.05 is considered statistically significant. Statistical analyses will be carried out exclusively by an independent statistician. All analyses will be performed by using SPSS, version 24 (SPSS).

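### Laboratory safety values get only correlation and a comparison of means, and are not linked to adverse events, so marked abnormalities in one to three subjects may not show in the reported laboratory result

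*Protocol article*

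**What the plan says.** Section 2.6 names two sources for safety. The first is laboratory testing: "Assessment of safety will be conducted by laboratory parameters". The second, in the same sentence, is the adverse events, serious or not, that subjects report. Table 1 (section 2.4.3) places the complete blood picture and the renal and liver tests under laboratory assessment, at screening and week 8 only. Each subject therefore has one value before treatment and one after it.

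Section 5.2 then fixes the method. It says "For laboratory parameters, Spearman’s coefficient correlation will be used for comparison with different parameters", followed by "one way ANOVA test for significant correlation between groups". The general rule in the same section reports measurement data per group and visit as mean ± SD, and sends data that are not normal to an unnamed non-parametric test.

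The one safety item in section 3.2 is "Adverse events (graded by CTCAE) related to study treatment". Section 4.2 defines the term broadly: "An adverse event is any undesirable medical event occurring in the subject within the trial period", whether or not it is related to the intervention. Adverse events are graded by CTCAE 4.0 (sections 2.6 and 4.2), listed and described, and compared between arms by χ² or Fisher's exact test (section 5.2).

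**The concern.** Harm seen in blood counts or in liver and renal tests is often confined to a few subjects with large changes. A mean ± SD and a test of means are poor tools for that pattern, because a few large values move the mean a little and widen the SD a lot. A Spearman coefficient between parameters does not show how many subjects became abnormal either.

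Adverse event reporting could supply the per-subject view, but the article does not connect the two. Section 2.6 lists laboratory parameters beside what subjects report, and no section says what happens to an abnormal value that causes no symptoms. Safety is one of the trial's two stated aims. A report that followed section 5.2 could state that liver function did not differ significantly between arms while up to three formula subjects had marked rises, with nothing in the laboratory results to show it.

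**Working it through.** **Inputs from the protocol article.** Section 5.1 gives 52 evaluable subjects, and 1:1 allocation gives n = 52/2 = 26 per arm. The test is two-sided at 5%. The article states no figure for laboratory safety, so there is none to reproduce.

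**Assumptions, not in the article.** A liver enzyme is lognormal with median 20 and log-SD 0.35 in both arms, with upper limit 40. Then k formula subjects are moved to about 5 or 10 times the limit, and no placebo subject is.

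**Step 1, arithmetic for 5 times the limit.** The unaffected mean is m = 20 × exp(0.35²/2) = 21.3. The unaffected SD is s = 21.3 × √(exp(0.35²) − 1) = 7.7. An affected value is 5 × 40 = 200, so D = 200 − 21.3 = 178.7.

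- Difference in means = kD/n
- Formula-arm variance ≈ [(n − k)s² + k(n − k)D²/n]/(n − 1)
- t = difference / √((formula-arm variance + s²)/n). With two arms, F = t², and the critical t on 50 df is 2.01.

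For k = 3 the difference is 3 × 178.7/26 = 20.6. The variance is (23 × 58.9 + 69 × 178.7²/26)/25 ≈ 3,444, so the SD is 58.7. Then t = 20.6/√((3,444 + 58.9)/26) = 20.6/11.6 = 1.78, which is below 2.01.

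**Step 2, the limit as D grows.** D cancels and t tends to √(k(n − 1)/(n − k)). This is 1.00, 1.44 and 1.81 for k = 1, 2 and 3, and √(100/22) = 2.13 for k = 4. Extreme values therefore cannot make ANOVA significant for k ≤ 3, but they do for k ≥ 4.

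**Step 3, simulation with the same assumptions, and Fisher's exact test on k versus 0 of 26.**

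| k | t from step 1 | Limiting t | ANOVA p < 0.05, 5 × limit | 10 × limit | Fisher p |
|---|---|---|---|---|---|
| 1 | 0.96 | 1.00 | about 0.05% | 0% | 1.00 |
| 2 | 1.41 | 1.44 | about 0.3% | 0% | 0.49 |
| 3 | 1.78 | 1.81 | about 9% | about 1% | 0.24 |
| 4 | 2.11 | 2.13 | about 67% | about 87% | 0.11 |
| 5 | 2.41 | 2.44 | about 99% | about 100% | 0.051 |

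At 3 times the limit, ANOVA flags four affected subjects in about 52% of trials and five in about 88%.

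**Step 4, the non-parametric fallback.** For k = 1 to 3 a rank test gives p < 0.05 in about 4% to 9% of trials (up to 10% in one run), close to the 5% false-positive rate.

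**Step 5, other assumptions.** With normal values (mean 22, SD 8, upper limit 40) and 29 per arm, ANOVA flags 1, 2 or 3 subjects at 5 times the limit in about 0.1%, 0.7% and 12% of trials. At 3 times the limit the figures are 1.6%, 5.2% and 19%.

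**The case against.** The strongest reply is that individual harm already has a route into the results. The definition in section 4.2 is broad enough to include a laboratory abnormality. If one is recorded as an adverse event, it is graded, listed, described and compared between arms. This stands, so a reader who infers that individual toxicity cannot appear in the results goes further than the article supports. What remains is that the article does not say such values are recorded as adverse events.

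A second reply is that shift tables and listings are commonly left to the analysis plan, which is not shown. This also stands: their absence, or the absence of a laboratory item in section 3.2, would not be a finding by itself. The point rests on the method that section 5.2 does fix.

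A third is that section 5.2 allows a non-parametric test, and data with such outliers would fail a normality check. It is unclear whether that fallback covers laboratory parameters, whose own sentence names ANOVA. Step 4 shows that it would help little.

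Three further inferences fail:

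- It is not generally true that a more extreme value is less likely to be flagged. That holds up to three affected subjects and reverses from four.
- Counts are not a more powerful test. At 4 versus 0 of 26, Fisher p is 0.11, while ANOVA usually reaches significance.
- Section 2.2.2 excludes subjects whose "liver/renal function exceeds the upper limit of the reference value by two times". That is an eligibility rule, and not reusing it at week 8 is no contradiction.

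**Conclusion.** The point holds in this form: the laboratory analysis fixed in section 5.2 does not suit a safety assessment, and the article does not link abnormal laboratory values to adverse events. Marked abnormalities in one to three formula subjects may therefore go unseen in the laboratory result. At 5 times the limit ANOVA would flag them in about 0.05% to 9% of trials. The percentages depend on the assumed distribution and size of rise, and different assumptions gave the same picture at that level. The limiting values of t depend only on k and n. With four or more affected subjects the means would usually give the signal. The matter concerns the safety report and leaves the primary efficacy analysis untouched.

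**What to change.** In section 5.2, for the complete blood picture and the renal and liver tests, keep means ± SD as description only and make this the safety summary:

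- a screening-to-week-8 shift table by arm;
- the number and percentage of subjects per arm newly outside the reference range or with a higher CTCAE grade;
- a listing of each such subject;
- the between-arm risk difference with an exact 95% CI, described as making cases visible and not as a powered test.

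In sections 3.2 and 4.2, state whether such values are also recorded as adverse events.

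The cost is a few sentences and one extra table with its listing. No samples, visits or subjects are added, because both measurements are already scheduled. The limit of the change is low power: against none on placebo, Fisher's test needs six affected subjects of 26 to reach p < 0.05 (p = 0.023). A non-significant difference in counts must not be reported as evidence of safety.
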